##### Health-Related Quality of Life (HRQOL) SF-8 (Short Form 8)

The HRQOL-SF8 is a validated health survey that measures quality of life, functional health, and well-being; the 2 major scales, physical health and mental health, are included. The HRQOL-SF8 has well-established psychometric properties [37] and contains 8 items with a 4-week recall period. Each item has a 5- or 6-point response range. Physical component summary (PCS) and mental component summary (MCS) measures are calculated by weighting each SF-8 item using a norm-based scoring method given in the instrument guidelines. Higher summary PCS and MCS scores indicate better health. Scores above and below 50 are considered above and below the average in general populations [38].

##### General Self-Efficacy

The GSE is a 10-item self-report measure of self-efficacy, the belief in one's competence to cope with a broad range of stressful or challenging demands [39]. It includes questions about one’s perceptions in the ease in which they stick to their aims and accomplish goals and to solve most problems if they invest the necessary effort. The GSE was included as a potential mediator/moderator variable related to any diet changes. It is a validated health scale correlated to emotion, optimism, and work satisfaction. Negative coefficients correlated to the GSE include depression, stress, health complaints, burnout, and anxiety. High reliability, stability, and construct validity of the GSE scale have been confirmed, and Cronbach alphas obtained for the GSE scale have ranged from .86 to .94 [40].

##### Measures of Change in Knowledge, Motivation, and Behavior

Three questions developed by the research team were included to assess for changes in knowledge, motivation, and behavior related to DNA-based dietary advice. These were based on review of the research literature and included questions about the stages of change model [41]. The questions were pilot-tested before use.

##### Anthropometrics

Baseline measures of height, weight, waist circumference, and hip circumference based on standardized protocols [35] are included. Body mass index (kg/m^2^) and waist-to-hip ratio will be calculated.

##### Covariates

Other relevant measures that can influence dietary intake and health behavior were assessed and controlled for. These included:

*Natural health product (NHP) usage:* NHP use (eg, vitamins, minerals, botanicals), which can influence nutrient intakes, is recorded at all study time points and included type, dose, and frequency of use. Participants were advised at baseline to keep any NHP use at the same dose and frequency throughout the study.*Physical and sedentary activities:* To measure activity level, physical activity index (PAI) [42] was used. The PAI included questions about the frequency, duration, and intensity of participation in certain activities in the previous 3 months. The data on physical activity were combined to obtain the PAI, which represents the average daily energy expended on leisure-time physical activity, expressed in kilocalories per kilogram body weight per day. To calculate this index, the energy expenditure (EE) for each activity was first estimated (see Multimedia Appendix 1 for details). The overall EE totals are used to categorize individuals as inactive (PAI <1.5 kcal/kg/day), moderately active (PAI 1.5 to <3 kcal/kg/day), and active (PAI ≥3 kcal/kg/day).*Sleep quality*: The Patient-Reported Outcomes Measurement Information System Sleep Disturbance scale-short form [43] is used to assess sleep quality. The instrument is an 8-item self-rated questionnaire, which assesses sleep quality over the previous 7 days. Individual items are scored on a scale from 1 to 5, and scores are summed to yield a total raw score between 8 and 40, with lower scores indicating better sleep or a lesser degree of sleep-related impairments.*Stress*: Because one’s ability to deal with stress can impact dietary intake, 2 validated questions from the Canadian Community Health Survey [44] are included as covariates.*Sociodemographics*: Standard determinants of health are measured that include sex/gender, age, relationship status, income, race/ethnicity, and perceived social support. The questions have been previously validated in studies such as the Canadian Community Health Survey.

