#### Recruiting/Screening: Online

Participants who entered the screening phase electronically signed an online informed consent form to grant permission to collect eligibility information and baseline health information (if deemed eligible). If the participant met the inclusion criteria, they were sent a 3-day food record to complete within 7 days (±3 days) of their first site visit. In addition, they were sent the link to complete an online baseline assessment questionnaire that collected information about sociodemographics, their health (eg, presence of any health conditions, medications, supplements used), health-related quality of life (Short-Form 8, SF8), self-efficacy (General Self-Efficacy, GSE), physical and sedentary activities, food intakes (food frequency, food selection), and sleep quality.

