#### Baseline Physical (On-Site) Visit

At the first visit, each participant met with the research team. They reviewed and signed a paper copy of the informed consent. The RD studied their online questionnaire information and did a nutrition assessment. Baseline measures of height, weight, and waist and hip circumference, based on standardized protocols [32], were performed. The 3-day food records were also reviewed to ensure completeness and accuracy.

At this stage of the study, a buccal swab cheek sample was obtained for gene testing. Buccal DNA samples were collected using Oracollect-DNA OCR-100 swabs (DNA Genotek, Ottawa, Canada). The RD collected the samples, identified with barcodes for confidentiality and blinding, and stored them between 15°C and 30°C. Participants did not eat or drink at least 30 min before obtaining their buccal swab. The samples were processed at the Clinical Genomics Centre at Mount Sinai Hospital in Toronto using Agena MassARRAY. Gene testing was done in 5 areas (Table 2) that were selected based on recommended evidence approaches to personalized nutrition [33].

Participants were informed that the processing time to receive results would be approximately 2 to 4 weeks. Between visits 2 and 3, a statistician independent to the study completed the randomization to the I and C group, using a computerized random generator.

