### Three- and Six-Week Online Check-Ins

At 3- and 6- weeks post intervention, both participants in I and C groups were sent their first follow-up online questionnaire with baseline measures repeated. Information about any adverse events (AEs), change in health status, and concomitant medication information was obtained. The only difference between the 2 questionnaires was that the I group questionnaire asked about whether knowing one’s personal DNA helped the participant choose specific foods and meals to eat healthier. After the week 6 check-in, participants were sent food records to complete and bring to the final on-site visit. At the time of writing, the study is just in the completion of this phase.

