#### Inferential Analysis

Inferential analysis includes Student *t* tests, analysis of variance (ANOVA), and Fisher exact tests to compare differences between groups and pre- and postinterventions. Analysis of the primary outcome measures involve conducting a series of repeated measures ANOVAs, comparing scores for each of the groups on the primary outcome measures (ie, food intake) at baseline and 8 weeks after receiving gene test results. The second set of analyses will involve using repeated measures ANOVAs to compare the 2 groups on measures of the different covariates. All analyses will be done on an intent-to-treat basis (last observation carried forward) using StataCorp’s STATA software [47].

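### Covariates are said to be controlled for, but the stated analysis has no adjusted model, does not fix which covariate values would be used, and has no test for the mediator/moderator role given to self-efficacy

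*Protocol article*

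**What the plan says.** **Role of the covariates.** The Covariates section introduces natural health product use, physical and sedentary activity, sleep quality, stress and sociodemographics with the statement "Other relevant measures that can influence dietary intake and health behavior were assessed and controlled for". The Inferential Analysis section lists t tests, ANOVA and Fisher exact tests. It describes the primary analysis as repeated measures ANOVAs of the primary outcomes by group, at baseline and 8 weeks after the gene results. No covariate term is named. The covariates enter once: "The second set of analyses will involve using repeated measures ANOVAs to compare the 2 groups on measures of the different covariates".

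**Timing.** The online baseline questionnaire collects sociodemographics, supplements used, "self-efficacy (General Self-Efficacy, GSE), physical and sedentary activities, food intakes (food frequency, food selection), and sleep quality". Randomization follows, between visits 2 and 3, when an independent statistician "completed the randomization to the I and C group, using a computerized random generator". After that, supplement use "is recorded at all study time points and included type, dose, and frequency of use", and at 3 and 6 weeks both groups "were sent their first follow-up online questionnaire with baseline measures repeated". Table 1 puts income and social support in a follow-up set ticked at V2, V4 and V5. For stress the article says only that "2 validated questions from the Canadian Community Health Survey [44] are included as covariates"; no time point is given.

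**Self-efficacy.** The General Self-Efficacy section says "The GSE was included as a potential mediator/moderator variable related to any diet changes". The Objectives give the same double label to changes in self-efficacy. The Abstract lists change in self-efficacy among the primary outcomes.

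**The concern.** A variable that appears only as a dependent variable has not been controlled for, so the two sections give the covariates different roles. An analyst could take an unadjusted, a baseline-adjusted or a follow-up-adjusted result from this text and cite the article for each.

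The choice matters because the intervention could plausibly move some of these variables. The gene test reports on vitamins and minerals, and the intervention arm receives dietitian counseling with personal nutrition goals. Supplement use or activity may therefore shift after randomization. Conditioning on a variable that the intervention has shifted removes the part of the effect that runs through it, and the result is no longer a plain randomized comparison.

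Self-efficacy raises a related problem. A moderator must be fixed before the intervention can act on it. Comparing the arms on self-efficacy tests neither mediation nor moderation.

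**Working it through.** The point concerns consistency, so there is no plan figure to reproduce. The stated minimum of 16 per group plays no part in it.

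**Step 1: the sections side by side.**

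| Item | Covariates / Objectives / GSE section | Inferential Analysis |
|---|---|---|
| Covariates | Controlled for | Compared between arms as dependent variables |
| Primary model | Not described | Group and time; no covariate named |
| Self-efficacy | Mediator/moderator | No mediation or interaction analysis named |

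**Step 2: which values exist.**

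| Covariate | Before randomization | After randomization |
|---|---|---|
| Supplement use | Yes | Yes, all time points |
| Activity, sleep | Yes | Yes, baseline set repeated |
| Income, social support | Yes (V2, Table 1) | Yes (V4, V5) |
| Age, sex, ethnicity | Yes | Cannot be changed by the intervention |
| Stress | Not stated | Not stated |

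Both kinds of value exist for most of the set, and no section says which is used.

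**Step 3: what the choice of value does (illustration).** Everything here is assumed except the arm sizes of 36 and 19, which come from the Abstract. Let T be the group, C0 the baseline covariate and C1 its follow-up value:

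- C1 = 0.5·C0 + √0.75·e1 + a·T
- Y = (0.80 − a·b)·T + b·C1 + √(1 − b²)·e2

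Here a is the shift that the intervention causes in the covariate (in SD), b is the covariate-outcome slope, and e1 and e2 are independent standard normal errors. The total effect is (0.80 − a·b) + a·b = 0.80. Adjusting for C1 leaves 0.80 − a·b. Mean estimates over 3,000 simulated trials per row:

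| a | b | 0.80 − a·b | Unadjusted | Adjusted for C0 | Adjusted for C1 |
|---|---|---|---|---|---|
| 0 | 0.3 | 0.80 | 0.807 | 0.808 | 0.806 |
| 0 | 0.5 | 0.80 | 0.798 | 0.797 | 0.797 |
| 0.3 | 0.3 | 0.71 | 0.796 | 0.795 | 0.706 |
| 0.3 | 0.5 | 0.65 | 0.796 | 0.795 | 0.648 |
| 0.5 | 0.3 | 0.65 | 0.805 | 0.804 | 0.656 |
| 0.5 | 0.5 | 0.55 | 0.797 | 0.797 | 0.547 |

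The loss is a·b: 0.09 to 0.25 SD where the intervention shifts the covariate, which is 0.09/0.80 = 11% to 0.25/0.80 = 31%. It is zero if the intervention does not shift the covariate, or if the baseline value is used. If a and b had opposite signs, the estimate would be inflated instead.

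**Step 4: self-efficacy.** GSE is measured before randomization, so a baseline moderator is available. The change in GSE arises after randomization; it can lie on the causal path but cannot define subgroups that randomization balances. A mediation analysis also needs GSE measured before the diet outcome. The section on the 3- and 6-week check-ins repeats the baseline measures at those weeks and sends out food records after week 6, which gives that order. Table 1 instead ticks the baseline set and the food records together at V5, 8 weeks after the consult, which does not. The two must be reconciled first.

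**The case against.** The strongest reply is that this is a condensed article. Its list of tests is introduced as what the analysis includes, so it need not be complete. Comparing arms on covariates does not rule out also adjusting for them, and the model terms may sit in an analysis plan that is not shown. Participants were also told to hold supplement use constant, which is a form of control by design and makes a shift less likely. Much of this stands: it rules out saying that the plan will never adjust. It does not remove the problem that the one role the analysis section gives the covariates differs from the role they were announced to have. The supplement advice covers one covariate only.

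A reader might go further in three ways that the documents do not support:

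- **That follow-up values are the ones to be adjusted for.** No section says so. Most of the set is also collected before randomization, and stress has no stated time point at all.
- **That the primary model is overloaded.** The Covariates section yields at least 1 + 1 + 1 + 2 + 6 = 11 variables (supplements, activity, sleep, two stress items, six sociodemographics) for 55 participants. Nothing says that they enter one model together, so the count is only illustrative.
- **That self-efficacy is simply mislabeled.** The label is mediator/moderator. The mediator half is legitimate for a change, and the GSE section attaches the label to the scale itself, whose baseline value could serve as a moderator. The fault is confined to offering a change as a possible moderator and to the lack of a matching test.

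**Conclusion.** The concern holds in this form. The article announces control for covariates, but its analysis section specifies no adjusted model and uses the covariates as outcomes. The time point of the covariate values is left open although several are re-measured after randomization. The change in self-efficacy is offered as a possible moderator, which it cannot be, and no listed test addresses mediation or moderation.

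The size cannot be taken from the documents. Bias arises only if follow-up values are used and the intervention moves them. The illustrative loss of 11% to 31% of a 0.80 SD effect rests wholly on the assumed shifts and slopes of 0.3 to 0.5. The trial is described as an exploratory pilot, which limits the consequences. The quantitative data had not been analyzed when the article was written, so settling the point beforehand prevents a choice guided by results.

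**What to change.** 1. **Covariates and Inferential Analysis:** reconcile the two. Analyze the 8-week primary outcome with adjustment for its baseline value and a short, named set of pre-randomization covariates. Include stress only if a pre-randomization measurement is confirmed.
2. **Follow-up covariate values:** state that they are not used as adjusters and that between-group comparisons of them are exploratory.
3. **Objectives and General Self-Efficacy:** test moderation as a baseline GSE-by-group interaction. Treat post-consult GSE only as a candidate mediator, in a separate exploratory analysis, after reconciling the GSE time points in the check-in section with those in Table 1.

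The cost is wording, fewer covariates in the primary model and a little more analysis work. Apart from confirming when stress was measured, the repair relies on data already scheduled for collection.

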##### Safety Reporting

At each study visit and online contact, participants were asked if they have experienced any AEs, change in health status, and/or had started any new medications or natural health products since the baseline visit. These data were captured using an AEs log and concomitant medication log.

### Data Analysis

#### Quantitative Analysis

##### Food Intake and Nutrient Analysis

Nutrient analysis was conducted using ESHA—The Food Processor Nutrition Analysis and Fitness Software [45] and the Canadian Nutrient File [46]. Three-day food records were manually entered by a trained research assistant and cross-checked by the coinvestigators. Averages of the 3 days of nutrient values were used in the analysis.

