### Description of Study Groups

Participants, who were deemed eligible and provided consent, were randomized by a statistician independent to the study into either the intervention or control group. Those randomized to the intervention (I) group received their gene test result report (standard) and an integrated report in paper and online format that integrated information about their gene tests, dietary intakes in relation to the standards, and personalized DNA-based diet plan as recommended by current guidelines regarding personalized nutrition [23]. They also received counseling by a trained research registered dietitian (RD).

The counseling provided by the RD was based on both reports outlining their genes, markers, and variants. It included a corresponding DNA-based diet recommendation. For example, those who possessed the genotype that has been associated with increased risk of a health outcome were provided a “targeted” dietary recommendation. Subjects not possessing the specified risk variant received the current standard dietary recommendations [5,28]. In addition, the RD worked collaboratively with the participant to define 1 to 3 nutrition-related goals they would work on. Both groups received 3 follow-up emails (one every 2 weeks post intervention) with information about nutrigenomics as well as tips and reminders (eg, information about label reading) to help them reach their nutritional goals.

After the study is complete, participants randomized to the control (C) group will receive the intervention, that is, they will receive DNA-based dietary advice at the final study visit. Therefore, they will receive the same benefits, if any, as those who had the full intervention.

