### Final Visit

At the final visit, the research team will review all data collected post intervention to ensure accuracy and completeness. The research dietitian will then conduct a repeat nutrition assessment. Participants in the C group will receive an individualized diet plan tailored to their health information and gene test results. Invitations to attend a focus group to solicit feedback about their experiences with the study will be extended. The interview guide for the focus group concentrates on collecting data about participants’ responses to their gene test results and RD consultation, how they used their results, suggestions for improvements, and impressions about barriers and facilitators in using their results.

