#### Nutrition Outcomes

Three-day food records measured pre- and postnutrient intakes including daily eating patterns. Changes in caloric, macronutrient, micronutrient, and food groups will be measured and compared with national standards (eg, *Eating Well with Canada’s Food Guide*, *Dietary Reference Intakes*). Changes in overall diet quality will be assessed using the Canadian version of the Healthy Eating Index [34]. Protocols for food record data collection will be derived from Health Canada nutrition survey procedures [35].

In addition to nutrient intake information collected from the food records, a food frequency questionnaire (FFQ) is included to assess for usual intakes and to validate the food record information. The food frequency measurement tools were derived from Health Canada nutrition survey measures [35].

Nutrition measures also included food selection questions about types of food selected, dietary restraint, food insecurity, motivation to change diet, and eating behavior changes. These were based on validated measures such as the Three Factor Eating Questionnaire [36], Health Canada, Statistics Canada (eg, the Canadian Community Health Survey), and BC Ministry of Health surveys [35], as well as review of the research literature about measurements of motivation and dietary change and eating behavior changes. Some of these questions were developed by the research team and pilot-tested for comprehension and face validity.

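### The final food records, source of the primary diet outcome, are reviewed, entered and cross-checked by staff who can know the arm, with no masking stated

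*Protocol article*

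**What the plan says.** For the main comparison, Inferential Analysis plans ANOVA with repeated measures, which it describes as "comparing scores for each of the groups on the primary outcome measures (ie, food intake) at baseline and 8 weeks after receiving gene test results". Nutrition Outcomes gives the source of the data: "Three-day food records measured pre- and postnutrient intakes including daily eating patterns".

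The final records reach the team late. After the week 6 check-in, "participants were sent food records to complete and bring to the final on-site visit". Final Visit then sets out the order of events: "the research team will review all data collected post intervention to ensure accuracy and completeness", followed by "The research dietitian will then conduct a repeat nutrition assessment". Control participants receive their individualised diet plan at the same visit.

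Under Food Intake and Nutrient Analysis, the records are "manually entered by a trained research assistant and cross-checked by the coinvestigators", using nutrient software and the Canadian Nutrient File.

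In the intervention arm a research dietitian gave the counselling, and "the RD worked collaboratively with the participant to define 1 to 3 nutrition-related goals they would work on" (Description of Study Groups). The follow-up questionnaires carry one extra item in that arm (Three- and Six-Week Online Check-Ins). The only blinding mentioned anywhere is in Baseline Physical (On-Site) Visit, where the buccal samples are barcoded.

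**The concern.** A handwritten or typed food record is not a finished measurement. Someone has to decide what portion was meant, which database food matches the entry, and whether an apparent omission should be queried. A review for accuracy and completeness, and the cross-check of entry, are the points at which such decisions are made. If the people making them can tell the arm, they may resolve doubtful items in the direction of the trial's hypothesis without intending to.

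Participants are unmasked and report their own intake, so the outcome is already open to one bias. Arm-related handling by staff would add a second, and this one is avoidable. Neither a larger sample nor a different model would remove it, because it would sit in the data as a difference between arms.

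**Working it through.** The article gives no figure on this point to reproduce. The check has two parts: which records are exposed, and how much a given shift would matter.

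**1. Exposure, step by step**

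- *Baseline review.* This takes place at the baseline visit. Randomisation follows, between visits 2 and 3. This review cannot be influenced by arm.
- *Final review.* Records are brought to the final visit and reviewed there by the research team. The arm can be known in two ways: the team must know who is due the control plan at that visit, and the review covers all post-intervention data, which includes questionnaires that differ by arm.
- *Entry and cross-check.* These are done by a research assistant and the coinvestigators. The article does not say that they know the arm. It also describes nothing that would prevent it.
- *Randomisation by an independent statistician.* This protects the allocation. It does not protect the later handling of outcome data.

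The exposure established by the text is therefore in the final records. A shift there passes in full into the change from baseline.

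**2. Illustration of size**

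Inputs: 36 intervention and 19 control participants (Abstract, Methods). Assumptions: two-sided 5% test, no true effect, and a differential shift of *b* SD from record handling. The documents give no value for *b*.

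With two groups and two time points, the group-by-time test in a repeated measures ANOVA is equivalent to a two-sample *t* test on the change. The SD here is therefore that of the change.

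- SE of the standardised difference = √(1/36 + 1/19) = √(0.0278 + 0.0526) = √0.0804 = 0.284
- Degrees of freedom = 36 + 19 − 2 = 53
- Noncentrality = *b* / 0.284

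| Assumed shift *b* (SD) | Noncentrality | Significant, either direction | Significant, favouring intervention |
|---|---|---|---|
| 0 | 0 | 5% | 2.5% |
| 0.1 | 0.35 | 6% | 5% |
| 0.2 | 0.71 | 11% | 10% |
| 0.3 | 1.06 | 18% | 18% |
| 0.4 | 1.41 | 28% | 28% |

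The rejection probabilities come from the noncentral *t* distribution. With masked handling the expected shift from this source is 0, which is the first row. The table shows sensitivity to an assumed shift. It is not evidence that a shift of any given size occurs.

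**The case against.** Several objections have force.

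- *The dietitian's part.* A reader might infer that the dietitian who counselled the intervention arm also reviews or codes its final records. The article does not say so. The review is assigned to the research team, the dietitian's repeat assessment is a separate and later step, entry and cross-check belong to others, and it is only implied that the same dietitian did both the counselling and the final assessment. This objection stands.
- *Knowledge of arm.* A reader might also infer that those who enter and cross-check the records know the arm. That is not stated. Only the weaker statement is supported: they can know it.
- *Order of the final visit.* The review already precedes the dietitian's assessment and the control plan. This helps, but it does not mask the reviewers, for the reasons given in the working.
- *Condensed article.* Masking of data entry may be described in the full protocol, which is not shown. That limits confidence. However, the point rests on a stated workflow, in an article that does mention blinding for the swabs.
- *Discretion.* Nutrient software and a standard food file constrain coding. They do not settle unclear portions or missing items.
- *Tense.* The entry and cross-check are described in the past tense while the final visit lies ahead, so some of that text may describe baseline work. Tenses are mixed throughout, and no different procedure is given for the final records.
- *Pilot status and self-report.* The trial is an exploratory pilot with unmasked participants, and masking staff leaves their reporting bias untouched. This is true, but it does not justify adding an avoidable bias.

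**Conclusion.** The point holds for the final food records. The source of the primary diet outcome is reviewed at a visit where the arm is evident, then entered and cross-checked, with no masking stated at any of these steps. Staff could therefore influence the comparison in favour of the counselled arm.

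The size of any such effect is unknown. The error rates of about 6% to 28% depend entirely on the assumed shifts of 0.1 to 0.4 SD. The documents do not support saying that bias has occurred, or that the counselling dietitian handles the records. They show no corresponding defect in the anthropometric measurements.

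Nor would it be right to say that masking costs nothing, or that all records should be recoded together. The intervention report integrates participants' dietary intakes and is delivered about 4 weeks after baseline, and the baseline records are the evident source. Their processing therefore cannot wait for the final records, and mixing the two sets would mean entering the baseline records again.

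Confidence is medium, because the full protocol might add masking. The change is worth making: it is cheap, and at the time of writing the final visit was still ahead.

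**What to change.** 1. Copy and lock each final food record on arrival, before the team's review, the dietitian's assessment and the control plan.
2. Log any later clarification separately, with the locked record left unaltered.
3. Extend the existing barcoding to the final records. The same research assistant and coinvestigators then enter and cross-check them under an ID code, without arm labels and in random order.
4. Link the codes to arm only after the nutrient file is frozen.

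Baseline records need not be recoded: they were reviewed before randomisation and are needed for the intervention report.

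*Cost:* relabelling, and a short delay or batching of final-record entry. The same staff do the work. The change does not address participants' own reporting bias, which the trial report should acknowledge separately.

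### Micronutrient intake set against the Dietary Reference Intakes is built from food records without the supplement doses that the trial also records, so total intake is understated for supplement users

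*Protocol article*

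**What the plan says.** All references are to the protocol article.

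- **Source of the outcome.** Nutrition Outcomes: "Three-day food records measured pre- and postnutrient intakes including daily eating patterns". The same section plans that "Changes in caloric, macronutrient, micronutrient, and food groups will be measured and compared with national standards", and gives the Dietary Reference Intakes as one example of such a standard.
- **Derivation.** Food Intake and Nutrient Analysis: "Three-day food records were manually entered by a trained research assistant and cross-checked by the coinvestigators". The records are run through nutrition software and the Canadian Nutrient File, and "Averages of the 3 days of nutrient values were used in the analysis".
- **Second source.** Nutrition Outcomes adds that "a food frequency questionnaire (FFQ) is included to assess for usual intakes and to validate the food record information". Food Frequency Analysis obtains each nutrient total by summing over the questionnaire's food items.
- **Supplements.** Covariates acknowledges that NHP use, with vitamins and minerals as examples, can affect nutrient intake, and states that it "is recorded at all study time points and included type, dose, and frequency of use". Participants were advised at baseline not to alter their use. NHP use stands in a list introduced by: "Other relevant measures that can influence dietary intake and health behavior were assessed and controlled for".
- **Monitoring.** Safety Reporting has participants asked at each contact whether they "had started any new medications or natural health products since the baseline visit".
- **Analysis.** Inferential Analysis compares the groups on food intake by repeated measures ANOVA, and in a second set of analyses compares them on the covariates.

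**The concern.** A reference intake for a vitamin or mineral is a level, and a person's intake of that nutrient includes what comes from a tablet. The article describes in some detail how nutrient values are obtained, from food records and from the questionnaire, and neither derivation has a supplement term. The NHP data that could supply the term are collected but given a different job.

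The gap matters here because the gene test covers 12 vitamins, minerals and essential fats (Table 2), and the Abstract lists nutrients among the primary outcome measures. Reporting how micronutrient intake stands against the Dietary Reference Intakes would make supplement users look less well supplied than they are, and any high total intake would go unseen. If supplement use also changed after results were received, and changed differently in the two arms, a food-only comparison would miss that part of the response.

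**Working it through.** The plan gives no figure to reproduce: there is no supplement rate, dose or mean food intake. The check is algebra on the described derivation, followed by labelled illustrations.

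**Definitions, per participant and nutrient, in units of the reference intake**

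- F = 3-day mean from food records
- S = daily amount from NHPs (dose × frequency)
- T = F + S = total intake
- The described analysis uses F.

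**1. Level.** Error = F − T = −S. This is non-zero for every user of a product that contains the nutrient.

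Assumed F = 0.60:

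| S (assumed) | T = F + S | Value used | Error |
|---|---|---|---|
| 0.25 | 0.85 | 0.60 | −0.25 |
| 0.50 | 1.10 | 0.60 | −0.50 |
| 1.00 | 1.60 | 0.60 | −1.00 |

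In the last two rows the total exceeds the reference while the analysed value lies below it.

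**2. Does covariate control repair the level?** No. Adjusting for NHP use alters a comparison between groups. It does not add S back to a value that is then set against a fixed standard. Inferential Analysis, moreover, describes comparing the groups on the covariates, not an intake model adjusted for NHP use.

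**3. Change from baseline.** Error = (F_post − F_pre) − (T_post − T_pre) = −(S_post − S_pre). With constant use, S_post = S_pre and the error is exactly 0. It is non-zero only for a participant who starts, stops or alters an NHP.

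**4. Between-group difference in change (intervention I minus control C).** Error = −(mean change in S in I − mean change in S in C). It is 0 whenever the mean change is equal in the two arms, even if that change is not zero. Illustrations with an assumed S = 0.50 per starter:

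| Who starts an NHP (assumed) | Mean change in S: I | Mean change in S: C | Error in I − C |
|---|---|---|---|
| Nobody, or equal proportions | equal | equal | 0 |
| 10% to 30% of I, none of C | 0.05 to 0.15 | 0 | −0.05 to −0.15 |
| 2, 4 or 6 of 19 in C, none of I | 0 | 0.053, 0.105, 0.158 | +0.053, +0.105, +0.158 |

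The control entries are k/19 × 0.50. With S = 1.00 they double to 0.105, 0.211 and 0.316. Which arm changes NHP use more decides the sign, and nothing in the documents decides between the rows.

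**The case against.** The strongest reply has four parts.

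**The food-only reading rests partly on silence.** The article never says that supplements are excluded. Food Intake and Nutrient Analysis is a short summary, and a fuller protocol or analysis plan might define a food-plus-supplement total. This limits the point to what is described. It does not remove it, because two derivations are spelled out without a supplement term and NHP use is expressly placed among the covariates.

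**Constant use cancels.** A reader might infer that change in micronutrient intake is misstated for supplement users in general. It is not. The advice at baseline was to keep NHP use unchanged, and under that advice the error in change is zero.

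**The direction is unknown.** A reader might also infer that food-only scoring flatters the practitioner arm, because self-driven controls would buy supplements while counselled participants change foods. The documents do not support this. Both arms receive the gene report, and counselled participants could as well be the ones who start products, which reverses the sign. Nor does the Safety Reporting question show that the investigators expected new products. It only asks about them.

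**Food-only intake is a legitimate target.** The hypothesis concerns diet and eating behaviour, Inferential Analysis names food intake as the primary outcome, and the Healthy Eating Index is about food. This stands in full: replacing food-only intake in the primary comparison would change the question. The reply does not reach the comparison with reference intakes, where the amount from all sources is what matters. It is also true that the article describes no classification of individuals as adequate or inadequate. But a reference intake can be compared only with a level, whether individual or group, and a group mean is short by the mean supplement dose.

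**Conclusion.** The concern holds in a limited form. As described, micronutrient levels set against the Dietary Reference Intakes understate total intake by the full supplement dose for every user, and covariate control does not correct this. The conclusion assumes that the derivation is carried out as the article describes and that the comparison is meant to show intake from all sources.

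Change from baseline is wrong only where NHP use changes. The trial contrast is biased only where mean NHP change differs by arm. Either could happen, since the advice to hold use constant came at baseline, about 4 weeks before results on 12 vitamins, minerals and essential fats were received. How often, and in which arm, cannot be determined from the documents, so the between-group figures above are illustrations and not estimates. The primary food-intake analysis and the Healthy Eating Index are not faulted.

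**What to change.** 1. State for each nutrition outcome whether it is food-only or food plus NHP.
2. For each micronutrient and time point with a food record, derive total intake = 3-day food mean + daily NHP amount (dose × frequency, converted to a daily amount) recorded at the same time point. Use this total for the comparison with the Dietary Reference Intakes.
3. Keep food-only intake for the Healthy Eating Index, food groups and the primary between-group food-intake analysis.
4. Report the between-group difference in change in total micronutrient intake alongside, as a supporting analysis. It will show whether NHP changes after baseline differed by arm and whether that alters the reading of the food-only result.

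The cost is coding the nutrient content of products whose type, dose and frequency are already recorded, plus one derived variable per micronutrient. The drawback is reliance on label content. No new data collection is needed, and the Abstract states that the quantitative data had not yet been analysed, so the definition could be fixed before analysis.
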